### Randomization

Central randomization based on interactive web response system (IWRS,Brightech Clinical Information Management System) is carried out by Peking University Clinical Research Institute, which is independent of the trial administration office. The allocation sequence is computer-generated 1:1 with dynamic randomization system and is stratified by tumor size and neck lymph node metastasis.

### Blinding

Allocation status cannot be blinded for the participants and investigators due to different treatment methods and the visibility of implanted I-125 seed in CT image. However, the primary outcome (response to treatment) will be evaluated by an independent assessment board. Further, all statistical analysis will be done by a statistician in Peking University Clinical Research Institute who is not affiliated with the trial.

### Intervention –implanationt of I-125 seed

All subjects who are assigned to the intervention group will receive I-125 seed permanent implantation in the study. The operation of I-125 seed implantation will be conducted at the department of Oral and Maxillofacial Surgery, Peking University School and Hospital of Stomatology. I-125 seeds will be ordered from the manufacturer 1–2 days before surgical operation. The placement of the I-125 seed was determined from CT scans with the use of a brachytherapy treatment planning system (BTPS; Beijing Atom and High Technique Industries, Beijing, China). The I-125 seed (model 6711; Jaco Pharmaceuticals Co. Ltd., Zhejiang, China) activity was 0.9-1.0U per seed and had a half-life of 59.6 days. Clinical target volume (CTV) is defined as gross tumor volume (GTV) and its surrounding potential sub-clinical focus or microscopic focus, and it is also divided as CTV1 and CTV2. CTV2, namely high risk area, is defined as primary tumor and around 10 mm, as well as drainage regions of involved lymph node. CTV2, namely low risk area, is defined at 5 to 10 mm beyond CTV2 and lymphatic drainage area which should be prevented by irradiation. The prescribed dose is 120 Gy for CTV1 and 140 Gy for CTV2. And it is commonly assumed that irradiation dose can accumulate to prescribed dose in 6 months.

A CT scan is obtained one week after seeds implantation. The CT images in combination with BTPS are used to detect the location, number and isodose plot distribution of seeds. Re-implantation can be considered if implant related deficiencies are identified, including asymmetrical distribution, shedding or movement.

### Control group – IMRT

All subjects who are assigned to the control group will receive IMRT in the study, which is done at the department of radiotherapy, Peking University Cancer Hospital & Institute. Prescribed dose for planning target volume and dose segmentation is computed with simultaneous integrated boost modulated radiation therapy. In each fraction of irradiation treatment, a specific dose is used for different target volume during the entire course of treatment. Totally, 70 Gy IMRT in 33 fractions (5 fractions per week) are prescribed to the GTV, 60 Gy/33 fractions to CTV2, and 56 Gy/33 fractions to CTV1.

### Initial screening, assessment and follow-up

After providing informed consent, potential participants will be asked standardized questions about their demographic characteristics and medical history. In addition, physical examination, electrocardiography, routine urine test, blood clotting function, urine β-human chorionic gonadotropin (HCG) for reproductive-age women, specialized examination, imaging examination, blood routine examination and biochemistry, pathological diagnosis and Karnofsky performance scale etc. will also be done and used for checking inclusion/exclusion criteria (Fig. 2).

**Fig. 2 Fig2:**
[figure not shown]
Observation, assessment, and follow-up schedule

After randomization, eligible participants will receive their treatment planning investigations and are followed-up following the same schedule for both intervention group and control group (Fig. 2) until recurrence, other malignancy or death is confirmed. Treatment duration is approximately 6–7 weeks for IMRT group. All the participants in both groups will be followed up at 2, 4, 6, 9, 12, 15, 18, 21 and 24 months after randomization, with specialized examination, imaging examination, blood routine examination and biochemistry, Karnofsky performance scale, recording of treatment and adverse events assessment done each time. Quality of life (QOL) scale will be assessed at 2, 6, 12, and 24 months. Forward radiation adverse reactions will be evaluated at each follow-up appointment except at 2 months after randomization. In addition, pathological diagnosis and PET/CT examination will be considered by the investigator if imaging examinations are inadequate to assess the primary outcome. Radioactive adverse events were classified by The National Cancer Institute-Common Terminology Criteria for Adverse Events (NCI-CTCAE) 4.0 standard. Chronic radioactive damages were classified by the criteria of Radiation Therapy Oncology Group/European Organization for Research and Treatment of Cancer (RTOG/EORTC), with common signs and severity recorded.

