### Outcomes

Assessment of efficacy will be carried out by evaluation of imaging examination at each follow-up. If applicable, response to treatment will be evaluated according to the RECIST criteria (version 1.1) and classified as complete response (CR), partial response (PR), stable disease (SD) and progressive disease (PD). 

The primary outcome is estimated as the difference between the intervention and the control group in local control rate in 1 year. Local control rate is judged to have been attained if there is no evidence of PD at the primary site based on imaging findings and clinical examination at follow-up. However, distant metastasis and second primary cancer are not belonged to PD at the primary site in accordance with RECIST criteria (version 1.1) [28].

Secondary outcomes are a) progression-free survival (PFS), defined as the time from randomization to the earliest occurrence of PD in whole body or death due to any cause; PD in whole body includes PD at the primary site, distant metastasis and second primary cancer; b) overall survival (OS), from the date of randomization to the date of death from any cause or last date when the participant is alive; c) QOL evaluated using the European Organization for Research and Treatment of Cancer QOL Questionnaire (EORTC QLQ-C30 and QLQ-H&N35) of Chinese version; and d) safety of treatment.

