### Statistical analysis

Analyses will be made using SAS statistical software (version 9.3, SAS Institute, Cary, NC, USA) by researchers at the Peking University Clinical Research Institute. The primary analyses will be done on an intent-to-treat basis and the last observation carry forward (LOCF) is used for missing values. Descriptive statistics will be used to summarize demographic and clinical characteristics of subjects randomised to the intervention and control group. The difference between two groups on demographic and clinical characteristics, response rate and drop-out rate will be compared using t-tests (or Wilcoxon rank sum test) and chi-square test/Fisher’s exact test as appropriate.

Primary outcome (local control rate in 1 year) analyses will be carried out using chi-squared tests. The survival curves (PFS and OS) are estimated by the Kaplan-Meier method, and log-rank test is used to test the null hypothesis that the respective curves are equal between the two groups. A two-sided significance level of 5 % is used. A covariance model will be used to compare the QOL between two groups by adjusting the difference of baseline. The incidence of adverse events between two groups is compared with the chi-square test/Fisher’s exact test.

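### Scheduled imaging can end before month 12 for events that are not board-confirmed local progression, and LOCF then counts the participant as locally controlled at 1 year

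*Protocol article*

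**What the plan says.** Four parts of the protocol article bear on this point.

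- **Initial screening, assessment and follow-up.** Both arms follow one schedule "until recurrence, other malignancy or death is confirmed". Two sentences later: "All the participants in both groups will be followed up at 2, 4, 6, 9, 12, 15, 18, 21 and 24 months after randomization", with imaging at each visit. The section adds that "pathological diagnosis and PET/CT examination will be considered by the investigator if imaging examinations are inadequate to assess the primary outcome".
- **Blinding.** "Allocation status cannot be blinded for the participants and investigators due to different treatment methods". As a safeguard, "the primary outcome (response to treatment) will be evaluated by an independent assessment board". The Discussion repeats this as a measure against observer bias.
- **Outcomes.** The primary outcome is local control at 1 year. "Local control rate is judged to have been attained if there is no evidence of PD at the primary site", on imaging and clinical examination. The section also says that "distant metastasis and second primary cancer are not belonged to PD at the primary site".
- **Statistical analysis.** The primary analysis is by intention to treat, and "the last observation carry forward (LOCF) is used for missing values".

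**The concern.** The events that end follow-up are not the events that settle the primary outcome. The primary outcome is settled early only by PD at the primary site, which the board judges. Follow-up ends on a wider set: any confirmed recurrence, any other malignancy, or death. Nothing in the stopping rule refers to the primary site or to the board.

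A participant can therefore leave the imaging schedule before month 12 with the primary outcome still open. The analysis then supplies the 1-year value by carrying the last reading forward. If that reading was not PD, the participant counts as a success.

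What is at stake is whether 1-year local control is observed or imputed for these participants, and whether imputation is equally common in the two arms. Treatment is open-label. The timing of treatment also differs: the article says that the I-125 dose accumulates over about 6 months, while IMRT takes about 6 to 7 weeks. The scans at months 2, 4 and 6 thus fall at different stages of treatment in the two arms, and there is no ground for assuming that early stops are balanced.

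**Working it through.** No figure in the plan depends on this rule. The sample size is not in question: 81% against 45%, two-sided 0.05 and 90% power give 36 per arm (pooled variance, no continuity correction), so 72 in total, and 72 / 0.8 = 90. The check is to trace the rules together.

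**Step 1. Do the two follow-up statements agree?** One ends follow-up at a confirmed event. The other sends all participants to every visit up to month 24. For a participant with another malignancy at month 6, the first cancels the month-9 and month-12 visits and the second requires them. A site could follow either.

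**Step 2. If the stopping rule is followed, which cases lose the month-12 reading while the outcome is open?** The visits before month 12 are at months 2, 4, 6 and 9.

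| Event ending follow-up before month 12 | Local failure under Outcomes? | Month-12 reading | 1-year value under LOCF |
|---|---|---|---|
| Recurrence, and the board finds PD at the primary site | Yes | Not needed | Failure, correctly |
| Recurrence called, and the board reads no PD at the primary site | No | Missing | Last non-PD reading, so controlled |
| Other malignancy (second primary) | No | Missing | Last non-PD reading, so controlled |
| Distant metastasis, if it counts as recurrence here | No | Missing | Last non-PD reading, so controlled |
| Death without local PD | No | Cannot exist | Outside this point |

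Events first confirmed at month 12 or later cost nothing for the primary outcome, because the month-12 scan has been taken.

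The second row needs the call to be made without the board. The third needs no disagreement at all, since the Outcomes section itself says that a second primary cancer is not PD at the primary site.

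**Step 3. Which way can the imputed value be wrong?** Within an arm, carrying a non-PD reading forward is right if the primary site would still have been controlled at month 12, and wrong if it would have progressed. The error can only raise that arm's rate. The effect on the difference between arms depends on which arm has more such participants and how many would have progressed. The documents give neither.

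**Step 4. Can a size be derived from the planning rates?** The rates imply 45 × (1 − 0.45) = 24.75 local failures with IMRT and 45 × (1 − 0.81) = 8.55 with I-125 by 1 year. An assumed disagreement rate could be applied to these counts, but the base would be wrong. Calls that the board rejects are not failures on the board-judged outcome, and other malignancies are not local failures either, so neither group is a subset of those counts. Failures first seen at month 12 would also have to be left out. No defensible size follows.

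**The case against.** The strongest objection is that the article never says who confirms recurrence. The board may be the confirming body, since it evaluates response and efficacy is assessed at each follow-up. The full protocol or a board charter, neither of them shown, may say so, as may the Fig. 2 schedule. This stands as far as it goes, and silence on who confirms would not be a finding in itself. It does not remove the point. The article states a stopping rule, the rule includes an event that the Outcomes section excludes from local failure, and it conflicts with the statement that everyone is followed to month 24.

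Three stronger readings are tempting and are not supported.

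- A reader might infer that the unblinded investigator ends imaging and so controls what the board can see. The investigator's only stated role here is to consider pathology or PET/CT when imaging is inadequate. That the investigator confirms recurrence is an inference. Moving those requests to the board would be a preference and is not needed to solve the problem.
- A reader might infer that participants stopped early have no 1-year outcome. They have one, through LOCF. The weakness is that it is imputed, and always as control when the last reading was not PD.
- A reader might infer that several percentage points of the IMRT rate are at risk. That needs a disagreement rate that the documents do not give and a base that does not fit.

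It is also fair to say that scans after a called recurrence may follow further treatment and be harder to interpret. This limits what continued imaging can recover, but an observed reading still tells more than one carried forward from months earlier.

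**Conclusion.** The point holds as a conflict in the follow-up rules with a consequence for the primary outcome. As written, follow-up may end before month 12 without board-confirmed PD at the primary site, and LOCF then records local control. For another malignancy this follows from the text alone, taking that term to include the second primary cancer named under Outcomes. For a called recurrence it holds only if someone other than the board can confirm it, which the article leaves open.

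Both routes assume that sites apply the stopping rule and not the all-visits sentence. The frequency may differ by arm because treatment is open-label. The size, and the net direction for the treatment comparison, cannot be computed from the documents.

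**What to change.** Reconcile the two statements under Initial screening, assessment and follow-up. Wording to the following effect would do:

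> Primary-site imaging continues on the existing schedule to at least month 12, or to death, unless the independent assessment board has confirmed PD at the primary site. This applies in both arms, whether or not recurrence elsewhere, another malignancy or a recurrence not confirmed by the board has been recorded.

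The change keeps the visit schedule and the definition of local control as they are. It limits the use of LOCF after such events to participants who truly cannot be imaged.

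The cost is small: protocol wording, and a few scans that are already in the 24-month schedule. The one operational burden is that the board must read suspected-PD scans as they arise and cannot leave them all for a single batch.

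### The rule ending follow-up at recurrence or other malignancy contradicts the 24-month schedule and the overall-survival definition; applied literally, it would censor survival informatively and leave some 12-month local outcomes unassessed

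*Protocol article*

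**What the plan says.** Under Initial screening, assessment and follow-up, both groups follow the same schedule "until recurrence, other malignancy or death is confirmed". Two sentences later the same section says: "All the participants in both groups will be followed up at 2, 4, 6, 9, 12, 15, 18, 21 and 24 months after randomization". The Abstract gives the same visit months with no stopping condition.

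Under Outcomes, OS is measured "from the date of randomization to the date of death from any cause or last date when the participant is alive". Progression-free survival (PFS) is "the time from randomization to the earliest occurrence of PD in whole body or death due to any cause". For the primary outcome, 1-year local control, the section says that "distant metastasis and second primary cancer are not belonged to PD at the primary site".

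Under Statistical analysis, "The survival curves (PFS and OS) are estimated by the Kaplan-Meier method, and log-rank test is used" to compare the arms. The primary analysis is by intention to treat, with last observation carried forward (LOCF) for missing values.

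**The concern.** A rule that ends follow-up at recurrence suits PFS, whose event has then occurred. It does not suit OS. If contact ends at recurrence, the last date known alive is roughly the recurrence visit, so the patient is censored just when the risk of dying is likely to rise. Kaplan-Meier and the log-rank test assume that censoring is unrelated to prognosis, which would fail here. It would also fail unequally, since the protocol's own rates imply far more local failure on IMRT. The OS curves would then mostly describe death without recurrence, and a survival difference acting through local control would be hidden.

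The primary outcome is exposed as well. A second cancer, or a distant recurrence if the undefined word recurrence includes it, would end follow-up although neither is local progression. Before month 12, that leaves the 1-year local status unassessed.

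**Working it through.** **1. The plan's own figure.** The documents give no OS figure. The sample size for the primary outcome reproduces. With p1 = 0.81, p2 = 0.45, mean 0.63, two-sided 0.05 and 90% power:

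n per arm = [1.960 × √(2 × 0.63 × 0.37) + 1.2816 × √(0.81 × 0.19 + 0.45 × 0.55)]² / 0.36² = (1.338 + 0.812)² / 0.1296 = 35.7, so 36 per arm and 72 in total. Then 72 / (1 − 0.20) = 90. This point does not affect it.

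**2. Inputs for OS under the literal reading.**
- From the protocol (Sample size estimation): 1-year local control of 81% and 45%, and 45 patients per arm. Constant monthly hazards of local progression: λ = −ln(0.81)/12 = 0.01756 (brachytherapy) and −ln(0.45)/12 = 0.06654 (IMRT).
- From the protocol: a 24-month horizon.
- Assumed, because the documents give no values: death without progression at d = 0.002 to 0.01 per month, the same in both arms; median survival after progression of 6 to 24 months (h = ln 2 / median). Drop-out, distant recurrence and second cancers are left out.

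**3. Formulas at t = 24 months.**
- Leaving follow-up at progression: λ/(λ+d) × (1 − e^(−(λ+d)t))
- Deaths seen if follow-up stops there: d/(λ+d) × (1 − e^(−(λ+d)t))
- True survival: e^(−(λ+d)t) + λ/(λ+d−h) × (e^(−ht) − e^(−(λ+d)t))
- Kaplan-Meier mortality under that censoring: 1 − e^(−dt), identical in both arms

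**4. Middle case, d = 0.005, median 12 months (h = 0.05776).**
- Brachytherapy: e^(−0.5414) = 0.582. Leaving at progression: 0.778 × 0.418 = 32.5%. Deaths seen: 0.222 × 0.418 = 9.3%. True mortality: 25.3%.
- IMRT: e^(−1.717) = 0.180. Leaving at progression: 0.930 × 0.820 = 76.3%. Deaths seen: 0.070 × 0.820 = 5.7%. True mortality: 48.0%.
- Kaplan-Meier would show 1 − e^(−0.12) = 11.3% mortality in each arm.
- Among 90 patients: 11.4 + 21.6 = 33.0 deaths, of which 4.2 + 2.6 = 6.8 are seen. Unobserved: 1 − 6.8/33.0 = 79%.

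**5. Full range.** Simulation: 400,000 patients per arm for deaths, 3,000 trials of 45 per arm for log-rank power.

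| d per month | Median survival after progression (months) | Deaths of 90, all followed | Deaths seen if stopped | Unobserved | Power, all followed | Power if stopped |
|---|---|---|---|---|---|---|
| 0.002 | 6 | 40.2 | 2.8 | 93% | 93% | 2.8% |
| 0.002 | 12 | 29.5 | 2.8 | 91% | 75% | 2.6% |
| 0.002 | 24 | 19.4 | 2.8 | 86% | 42% | 2.9% |
| 0.005 | 6 | 43.3 | 6.7 | 84% | 88% | 4.5% |
| 0.005 | 12 | 33.0 | 6.8 | 79% | 62% | 4.9% |
| 0.005 | 24 | 23.0 | 6.7 | 71% | 28% | 4.6% |
| 0.01 | 6 | 48.2 | 12.9 | 73% | 77% | 5.6% |
| 0.01 | 12 | 38.1 | 12.8 | 66% | 44% | 5.2% |
| 0.01 | 24 | 28.6 | 12.9 | 55% | 16% | 4.3% |

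Across the grid, 31% to 34% of brachytherapy and 73% to 78% of IMRT patients leave at local progression. Kaplan-Meier mortality would be 5% to 21% in both arms, against true values of 14% to 39% (brachytherapy) and 29% to 68% (IMRT). Power near 5% or below is what this model must give: with the same d in both arms, the censored comparison has no difference left to detect.

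**6. Primary outcome.** Take a patient with a second cancer at month 4 and no local progression. The stopping phrase ends visits, the month-12 local status is missing, and LOCF carries forward no progression, so the patient counts as controlled. Each such patient can move an arm's rate by up to 1/45 = 2.2 percentage points. The documents give no frequency for these events, so the total effect cannot be sized.

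**The case against.** A reader might infer that deaths after recurrence will never be observed and that the OS comparison is worthless. The documents do not support that. Nowhere do they say that OS is censored at recurrence or that vital status is not collected afterwards. The 24-month sentence and the Abstract point the other way, and the OS definition refers to a date alive, not to a last visit. The stopping phrase may govern only the visit schedule of examinations, imaging and blood tests. Figures 1 and 2 are not available in the text reviewed and may show survival follow-up. An article may also leave the mechanics of survival contact to the full protocol.

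This stands as far as it goes: the finding is a contradiction, not a settled plan to lose deaths, and the absence of a described survival contact is not itself a fault. It does not remove the contradiction. The 24-month sentence may just list the dates of the schedule that the stopping phrase cuts short, so a site could reasonably apply either reading.

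Three further limits also stand. OS is secondary and the trial was not sized on it; PFS is unaffected by stopping at its own event. The death rates are assumptions. The Background describes many of these tumours as slow-growing with a long course, which favours the longer survival times, where power is low even with complete follow-up. And only other malignancy is named explicitly; counting distant recurrence is an interpretation.

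**Conclusion.** The concern holds as an internal contradiction that should be fixed. The follow-up section conflicts with itself and with the OS definition. The size of the harm depends on the literal reading being carried out and on the assumed death rates. On that footing, more than half of the deaths would be missed (55% to 93%), unequally by arm, and log-rank power for OS would be about 3% to 6%. That power figure also rests on equal death rates without progression in the two arms. If vital status is collected in everyone to 24 months, none of this loss arises. The effect on the primary outcome is real in principle under the same reading, but cannot be sized from the documents. The sample size and the primary test are unchanged.

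**What to change.** Replace the stopping phrase with a statement such as: vital status is collected for all randomised participants to 24 months after randomisation, regardless of recurrence or other malignancy; the scheduled primary-site assessments continue to month 12 or local progression, whichever comes first, including after distant metastasis or a second primary cancer. If the sponsor already intends this, the amendment only says so.

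The cost is a short amendment, vital-status contacts after recurrence, and completion of already scheduled primary-site assessments in a few patients. No extra patients are needed.
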